#### Experimental group

The experimental group will implement one-on-one online family resilience intervention on the basis of usual care. Intervention implementation will be led by a professionally trained nursing graduate student and a breast cancer-related unit nurse. A breast cancer therapist and a psychobehavioral specialist will guide and supervise the implementation of the intervention. The entire intervention process includes a preintervention program introduction, six family meetings, and a postintervention summary. The frequency of interventions is weekly, with each meeting lasting 25–30 min. The first meeting, combined with patient follow-up time, will be an face-to-face family meeting with participating families, and the next five meetings will be online family meetings. The first follow-up visit to the hospital after surgery is usually approximately 1 week after surgery. A quiet, undisturbed environment will be chosen for family meetings. The specific time for each family meeting must be agreed upon in advance with participating families.

Before the intervention begins, the researcher will brief the intervention group families about the program and build a relationship of trust with them. Assessors will collect baseline data, and another researcher will teach participants to use online video software. The first family meeting will be held 1 week after the patient’s surgery, and the theme will be understanding breast cancer and family resilience. The second family meeting will be held 2 weeks after surgery, and the theme will be remaining positive. The third family meeting will be held 3 weeks after surgery, and the theme will be discovering available resources. The fourth family meeting will be held 4 weeks after surgery, and the theme will be improving family cohesion. The fifth family meeting will be held 5 weeks after surgery, and the theme will be facilitating effective communication. The sixth family meetings will be held 6 weeks after surgery, and the theme will be family problems and coping. The themes of the six meetings stemmed from Walsh’s family resilience framework. The themes for the first and second meetings were from the belief systems, the themes for the third and fourth meetings were from the organizational patterns, and the themes for the fifth and sixth meetings were from the communication/problem-solving process. Formation of the main contents of the six-week intervention plan through a literature review. Then, the form and content of the intervention plan were adjusted through structured interviews with patients, family members, and medical staff in breast cancer-related departments. Finally, through two rounds of expert consultation, the content of the intervention plan was revised to ensure the scientificity and feasibility of the intervention plan.

One day before each meeting, meeting materials will be sent to the participants of the intervention group to inform them of the content of the meeting in advance. Two to 3 min before each meeting, there will be a review to summarize the content of the previous meeting. During the meeting, families of the intervention group will be guided to actively participate in the discussion through videos, pictures, questions, etc., to increase participation. After the meeting, participating families will be encouraged to review the content of the meeting through homework to improve the effect of the intervention. One week after the end of the intervention, participating families will be invited to assess the entire intervention process, and the assessors will collect postintervention data and give gifts to families to show appreciation for their participation. Details of the intervention plan are shown in Table 1.

**Table 1 tab1:** Outline of the coping-focused family resilience intervention program (CFFRI).

Unbreakable Belief - Know yourself and the enemy (First week after surgery)	
Theme	Understand Breast Cancer and Family Resilience
Form	Face-to-face family meeting
Target	Learn about breast cancer and how it affects families. Understand the concept and meaning of family resilience.
Content	Ask the patient and primary caregiver to share some of their questions and concerns after patients becomes ill. Explain breast cancer related knowledge to patients and their families in the form of pictures, text and videos. Combine video materials and family discussions to help family members understand the characteristics of breast cancer families and help each family member understand the changes in family roles. Explain the definition and importance of family resilience to patients and their families in a graphic and textual manner.
Homework	Review the content of this meeting through electronic meeting materials. Patients and primary caregivers share with researchers their views on breast cancer and the main effects of the disease on themselves or their families (*via* voice or text message or phone call).
Unbreakable Belief - Face with smile (Second week after surgery)	
Theme	Remain Positive
Form	Online family meeting
Target	Breast cancer treatment, life and psychology and other aspects care and precautions. Master the basic methods to relieve stress and soothe emotions.
Content	A brief recap of last week’s meeting. Let the primary caregiver to review issues encountered during the patient’s care over the past week. Combined with pictures and texts, it provides nursing methods and precautions for different treatments for breast cancer patients and their families. Have patients and primary caregivers share their emotions and stress over the past week. Help patients and primary caregivers learn ways to manage stress and emotions to stay positive and optimistic by combining pictures, text and videos.
Homework	Review the content of this meeting through electronic meeting materials. Patients and primary caregivers are encouraged to discuss their own stressors and ways to relieve stress with researchers (*via* voice or text message or phone call).
Family Organization - Family treasure (Third week after surgery)	
Theme	Discover Available Resources
Form	Online family meeting
Target	Identify the family’s own strengths and available resources and learn how to use them. Summarize the experience of overcoming difficulties from past experiences.
Content	A brief recap of last week’s meeting. Combine pictures and words to show participants’ families what family resources, social resources and family strengths are. Help family members discover and demonstrate their family strengths and resources. Discuss success and failure cases and their characteristics in overcoming difficulties through family conversations, and summarize experiences. Discuss together how to leverage existing family strengths and resources to address current issues and challenges. Encourage different families to exchange experiences through WeChat groups and provide emotional support to each other.
Homework	Review the content of this meeting through electronic meeting materials. Give researchers examples of how their resources will be used in the future (*via* voice or text message or phone call).
Family Organization - Intimacy has a way (Fourth week after surgery)	
Theme	Improve Family Cohesion
Form	Online family meeting
Target	Create simple and effective family rules to promote family relationships and strengthen family bonds.
Content	A brief recap of last week’s meeting. Combine pictures, text and video to show patients and primary caregivers what family rules are and how they work, and encourage patients and families to share existing family rules. Through family discussions, according to the specific situation of each family, clear and effective family rules are jointly formulated to enhance family interaction, strengthen family bonds, and promote family relationships.
Homework	Review the content of this meeting through electronic meeting materials. Patients and primary caregivers share with researchers their family relationship status, understanding and feelings about family rules (*via* voice or text message or phone call).
Communication and Coping - Rational communication (Fifth week after surgery)	
Theme	Facilitate Effective Communication
Form	Online family meeting
Target	Understand what communication is and what communication problems families have. Learn effective communication skills.
Content	A brief recap of last week’s meeting. Combined with video, show a case of quarrel caused by improper communication. Combine pictures and videos to show patients and primary caregivers what communication is, and the types of family communication. Through family discussions, help participating families identify problems in family communication and why they arise. Introduce effective communication skills to participating families by combining pictures and videos.
Homework	Review the content of this meeting through electronic meeting materials. Patients and primary caregivers share a successful communication case with researchers (*via* voice or text message or phone call).
Communication and Coping - Through thick and thin (Sixth week after surgery)	
Theme	Family Problems and Coping
Form	Online family meeting
Target	Learn general ideas for problem solving. Develop a plan to address current family issues. Summarize the entire intervention process.
Content	A brief recap of last week’s meeting. Identify existing family issues through family discussions. Combine pictures, text, and video to show patients and their families the general steps to resolve family problems. Co-exploring solutions to existing family problems following the problem-solving approach. A brief summary of the entire intervention process.
Homework	Review the content of this meeting through electronic meeting materials. Patients and primary caregivers share a case of collaborative problem-solving with researchers (*via* voice or text message or phone calls).

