## Materials and methods

### Study design

Due to the nature of the experiment, the interventionists could not be blinded in this study, so this study used a single-blind randomized controlled trial. Subjects will be included in the study in strict accordance with the inclusion and exclusion criteria. Eligible patients and their families will be included in the study according to their wishes. Participating families will be randomly divided into a control group and an experimental group according to computer-generated random numbers, with a distribution ratio of 1:1 (Figure 1). The control group will receive usual care. The experimental group will receive a family resilience intervention on the basis of usual care that will blind participants, recruiters and data collectors. This study constructs a family resilience intervention plan for breast cancer patients in strict accordance with the SPIRIT 2013 and CONSORT 2010 statement (Chan et al., 2013; Eldridge et al., 2016).

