### Sample size

Study sample size calculated by PASS15. Based on previous survey results (Lim and Han, 2013), family resilience measured by the Family Resilience Index (FHI) changed by 0.29 points before and after the intervention with a statistical power of 0.9, 2.5% significance, and using a one-tailed test to calculate a sample size of 36 families in each group (72 families in total; McCubbin et al., 1996). Assuming a 10% dropout rate in the intervention, each group would need to include 40 families (80 families in total). The sample size calculation formula is as follows:

$$n=\frac{{\left({Ζ}_{\alpha }+{Ζ}_{\beta }\right)}^{2*}2\sigma^{2}}{\delta^{2}}$$

A series of measures will be taken to reduce attrition during the intervention. First, during the intervention recruitment phase, the patient’s attending physician or other medical staff will be invited to answer the patient’s and family’s concerns to increase participants’ trust in the program. Second, a WeChat group will be established where researchers answer questions and share disease-related knowledge with participants. The third is to invite breast cancer treatment experts and nursing experts to control the quality of the entire intervention process, and timely answer questions from patients and their families about disease treatment and care. Fourth, during the intervention, participants can get in touch with the research team to get answers to any difficulties involved in the implementation and application of the intervention content. Finally, at the end of the program, the research team will present the participants with a nice gift to express their gratitude.

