### Randomization

Eighty random numbers will be generated by a computer and randomly divided into an intervention group and a control group with a distribution ratio of 1:1. The assigned numbers will be sealed in 80 opaque envelopes. Recruiters will enroll research subjects who meet the research conditions, agree to participate in the research, and sign an informed consent form. Subjects will randomly draw envelopes, enter their assigned groups, and have baseline measurements taken. Participant recruitment and assignment will be done by two independent researchers, blinding participants, recruiters and data collectors.

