### Data collection

First, the researcher will introduce the purpose of the study to the patients and their families and establish a trust with them. After obtaining informed consent from patients and their families, their baseline data will be collected. Baseline data includes sociodemographic data, clinical disease characteristics, and psychosocial variables. Psychosocial variables include family resilience, coping styles, family disease burden, social support, levels of anxiety and depression. Investigators will measure psychosocial variables of participating families at four time points: baseline and 1 week, 1 month, and 3 months after intervention (Table 2). Participants will be assured that all data and intervention processes will be confidential. Only the main researchers will have access to the final trial dataset.

**Table 2 tab2:** Data collection note.

	Outcomes	Baseline	1 week post-intervention	1 month follow-up	3 month follow-up
Eligibility criteria	Demographic and clinical data	√			
Primary outcome	Family resilience	√	√	√	√
Secondary outcome	Coping style	√	√	√	√
	Social support	√	√	√	√
	Family disease burden	√	√	√	√
	Anxiety	√	√	√	√
	Depression	√	√	√	√

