### Limitations

This study may have some limitations. First, there are many family meetings in the intervention program, and subjects may not be able to attend all of them due to physical or other reasons, which will lead to sample loss that may have an impact on the study results. Second, because of the nature of the study, it was not possible to blind the interventionists. Therefore, this study will arrange for independent researchers to collect and evaluate the data. Finally, while each family meeting will be held in an isolated quiet setting, some subjects may be contaminated due to subject recruitment and the first family meeting being held in the same department of the hospital. Therefore, when arranging meetings for families in the intervention group, researchers should try to choose an appropriate place and time to avoid crowd gathering and contamination between study subjects.

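### Programme evaluation, outcome collection and gifts share the 1-week time point, which puts the stated blinding of data collectors at risk; the gift also precedes the last two assessments

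*Protocol article*

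**What the plan says.** The Experimental group section plans that, one week after the programme finishes, "participating families will be invited to assess the entire intervention process, and the assessors will collect postintervention data and give gifts to families". The assessors thus both collect the post-intervention data and hand over the gifts.

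Three other places describe blinding or independence:

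- Study design describes a procedure "that will blind participants, recruiters and data collectors".
- Randomization states: "Participant recruitment and assignment will be done by two independent researchers, blinding participants, recruiters and data collectors".
- Limitations accepts that those delivering the programme cannot be blinded, and gives as the remedy that "this study will arrange for independent researchers to collect and evaluate the data".

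On incentives, Sample size lists measures against attrition during the intervention. The last of them is that "at the end of the program, the research team will present the participants with a nice gift". Setting and recruitment also offers gifts and free medical examinations to recruited subjects, without saying when. The Control group section mentions no gift and no evaluation.

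Data collection and Table 2 schedule the outcomes at "baseline and 1 week, 1 month, and 3 months after intervention".

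**The concern.** The control arm has no programme to evaluate. If families evaluate the programme in the presence of the person who collects their outcome questionnaires, that person learns the arm. The article offers independent, blinded collection as its protection against unblinded interventionists, so the protection would be weakened at the first measurement after the intervention.

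There is also a possible response effect. The outcomes are questionnaire answers from the families. Being asked to judge the programme, and being thanked with a gift by the assessors, at about the time they rate their own resilience, coping and mood could push those ratings in the programme's favour. That is the direction in which the trial tests, one-sided at 0.025.

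The third strand is retention. A gift listed as a measure against attrition is given before two of the three post-baseline assessments, and those two show whether an effect lasts.

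**Working it through.** **1. The sections side by side.**

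| Section | What it fixes | What it leaves open |
|---|---|---|
| Experimental group | Evaluation, outcome collection and gifts all at 1 week; assessors collect the data and give the gifts | Whether this is one visit; who takes the evaluation; the order of the steps |
| Study design; Randomization | Data collectors are blinded | How this is maintained at the 1-week time point |
| Limitations | Independent researchers collect and evaluate the data | Whether they are kept away from the evaluation |
| Control group | Usual care | Whether these families get the same gift, and when |

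The first row can be squared with the second and third only if the evaluation is kept apart from the assessors. The article does not say that it is.

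**2. Timeline (Experimental group; Data collection).** The sixth meeting is 6 weeks after surgery.

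- 1-week assessment and gift: 6 + 1 = week 7.
- 3-month assessment: 6 + 13 = about week 19.
- Time after the gift: 19 − 7 = about 12 weeks, containing two of the three post-baseline assessments.

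**3. Dropout allowance (Sample size).** The plan's own figure reproduces: 36 / (1 − 0.10) = 40 per group. The 10% is stated for dropout in the intervention. The article gives no SD. Solving its formula for the SD that yields 36 per group, with δ = 0.29, one-sided alpha 0.025 and power 0.90:

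σ = 0.29 × √[36 / (2 × (1.960 + 1.282)²)] ≈ 0.380, so δ/σ ≈ 0.76.

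This SD is an assumption of the check, not a figure in the plan. With 40 randomised per group and power = Φ(0.764 × √(n/2) − 1.96):

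| Total loss (assumed) | n per group | Power |
|---|---|---|
| 10% | 36 | 90.0% |
| 20% | 32 | 86.4% |
| 30% | 28 | 81.6% |

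Extra loss during follow-up would therefore cost some power. Nothing in the article says how much loss to expect, or that moving the gift would prevent it.

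**4. Sensitivity to a response shift.** The documents give no size for such a shift. Suppose there is no true effect, 36 families per group, and a shift of b SD in favour of the intervention in a single two-group comparison. The one-sided error rate is then P(Z > 1.96 − b/√(2/36)), with √(2/36) = 0.236:

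| b (assumed) | Error rate |
|---|---|
| 0 | 2.5% |
| 0.1 | 6.2% |
| 0.2 | 13.3% |
| 0.3 | 24.6% |

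This shows how sensitive a trial of this size is to small shifts. It does not estimate what the 1-week arrangement does.

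**The case against.** **Unblinding is inferred.** The article names no one as collecting the evaluation. It gives a time point, not a single encounter, and elsewhere it splits tasks: at baseline the assessors collect data while another researcher teaches the software. This stands. The text supports a risk of revealing the arm, not the statement that assessors will learn it.

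**The order is not stated.** A reader might infer from the order of the clauses that families judge the programme before they answer the questionnaires. Clause order is not procedure. If the questionnaires come first, most of the response effect at that time point falls away.

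**The control arm's gift.** A reader might infer that only intervention families are given gifts. Setting and recruitment and Sample size speak of subjects or participants in general, so this is not established. Only the evaluation clearly lacks a control-arm counterpart.

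**Incentives.** A reader might infer that nothing is left to keep families in follow-up. Setting and recruitment offers gifts and examinations with no timing, and the WeChat group has no stated end. A condensed article may also leave retention detail to the full protocol. What remains is narrow: the one gift whose timing is stated comes before the last two assessments, and nothing is tied to those.

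**The error rates.** A reader might take 6% to 25% as the cost of this arrangement. They cannot be read that way. The shift is assumed, and the calculation is for one comparison at one time point, whereas Statistical analysis plans repeated measures ANOVA. Families who attended six meetings rate themselves, so much of any gratitude or expectation effect would exist whatever the order of steps. For the same reason, an assessor's knowledge of the arm has limited leverage on self-completed scales.

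**The fix.** If the intervention team collects the evaluation, families may answer politely. That affects the evaluation, which Table 2 does not list as an outcome; it does not affect the trial's outcomes.

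**Conclusion.** The point holds as a conflict to be reconciled and a cheap improvement in design. As written, the 1-week procedure is not separated from an evaluation that only one arm can give, and this sits badly with the blinding in Study design and Randomization and with the safeguard in Limitations. It may also encourage favourable self-ratings at the first post-intervention measure of the primary outcome.

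The size of any bias is unknown. Whether it arises depends on who takes the evaluation and in what order, and neither is stated. The documents do not support a claim that the blinding will fail, that gifts go to one arm only, that follow-up has no incentive, or that the false-positive rate rises by a given amount.

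On retention, the timed gift falls about 12 weeks before the last assessment and no measure is stated specifically for the 1- and 3-month assessments. This reading takes the end of the programme in Sample size to be the end of the intervention, which agrees with the 1-week timing in the Experimental group section.

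**What to change.** Reconcile Study design, Sample size, Randomization, Experimental group and Limitations so that they state one procedure:

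1. At every time point, families in both arms complete the outcome questionnaires first, with assessors who take no part in the programme evaluation.
2. Existing staff who are not assessors collect the programme evaluation separately, preferably after the 3-month questionnaires.
3. Both arms receive the same end-of-study gift, after the 3-month assessment.

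This reorders existing steps and needs no new staff or visits. The downside is that programme feedback comes about 3 months later and may be less detailed. The change will not remove the expectation effects that come from families knowing that they took part in the meetings.
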